### Analysis of safety outcomes

All participants in the safety set are examined during safety analysis. All AEs that occurred during the intervention period are recorded, including their type, severity, frequency, and relationship to the intervention medicine. The quantity and frequency of adverse events are calculated for both groups. Severe adverse events and consequent drug discontinuation are meticulously recorded. Safety analysis will use qualitative judgment to define the distribution, counting the number of participants and their fraction of abnormal indicators using cross-tabulation (Table 5). The correlation between AE and medications will be evaluated using standards from the 2011 Ministry of Health of the People's Republic of China's Measures for the Reporting and Monitoring of Adverse Drug Reactions.

**Table 5 T5:** Analysis of the adverse events in the full analysis set.

Adverse event	SHHS Group (n=xx)	LHQW Group (*n*=xx)	*P-Value*
In total^b^	xx(xx%)	xx(xx%)	.xx
Headache^b^	xx(xx%)	xx(xx%)	.xx
Nausea^b^	xx(xx%)	xx(xx%)	.xx
Vomiting^b^	xx(xx%)	xx(xx%)	.xx
Diarrhea^b^	xx(xx%)	xx(xx%)	.xx
Loss of appetite^b^	xx(xx%)	xx(xx%)	.xx

^b^Number, percentage.

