**Methods and analysis:** The study was designed as a 7-day, randomized, parallel controlled, open-label, noninferiority clinical trial of positive drugs. A total of 240 patients with mild and moderate COVID-19 will be enrolled and randomly assigned to receive SanHanHuaShi granules or LianHuaQingWen granules treatment in a 1:1 ratio. Disease classification, vital signs, SARS-CoV-2 nucleic acid testing, symptoms, medications, adverse events, and safety evaluations will be recorded at each visit. The primary outcome will be the clinical symptom recovery rate. Secondary outcomes will include the recovery time of clinical symptoms, negative conversion time of SARS-CoV-2 nucleic acid test negative conversion rate, hospitalization time, antipyretic time, rate of conversion to severe patients, and time and rate of single symptom recovery. Adverse incidents and safety assessments will be documented. All data will be analyzed using a predetermined statistical analysis plan, including our method for imputation of missing data, primary and secondary outcome analyses, and safety outcomes.

**Discussion:** The results of this study will provide robust evidence to confirm the effectiveness and safety of SHHS in the treatment of COVID-19.

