Through modern pharmaceutical technology, the Chinese medicine decoction is extracted, concentrated, dried and shaped into a granular formulation. The quality control analysis of SHHS granules utilizing HPLC is provided by Jiangsu Kanion Pharmaceutical Co., Ltd. The quality control data and preliminary identification of the main components are available in **Additional file 1**. The daily dosage of SHHS granules is as follows: Houpo (*Magnolia officinalis* Rehd.et Wils.): 3.13g (equally 15 g herb medicine, abbreviated as 15 g), Jiaobinglang (*Areca catechu* L.):1.88g (9g), Caoguo (*Amomum tsao-ko* Crevost et Lemaire): 9g (1.88g), Mahuang (*Ephedra sinica* Stapf):6g (1.25g), Kuxingren (*Prunus armeniaca* L.var.*ansu* Maxim.): 9g (1.88g), Qianghuo (*Notopterygium incisum* Ting ex H.T.Chang): 15g (3.13g), Shengjiang (*Zingiber officinale* Rosc*.*): 15g (3.13g), Guanghuoxiang (*Pogostemon cablin*(Blanco) Benth.): 15g (3.13g), Peilan (*Eupatorium fortunei* Turcz*.*): 9g (1.88g), Cangzhu (*Atractylodes chinensis*(DC.) Koidz.): 15g (3.13g), Fuling (*Poria cocos*(Schw.)Wolf): 45g (9.38g), Baizhu (*Atractylodes macrocephala* Koidz.**):** 30g (6.25g), Shigao (*Gypsum Fibrosum*): 15g (3.13g), Jiaoshanzha (*Crataegus pinnatifida* Bge.var.*major* N.E.Br.): 9g (1.88g), Jiaomaiya (*Hordeum vulgare* L.): 9g (1.88g), Jiaoshenqu (*Massa Medicata Fermentata*): 15g (3.13g), Dilong (*Pheretima aspergillum* (E.Perrier)): 15g (3.13g), Xuchangqing (*Cynanchum paniculatum*(Bge.)Kitag.): 15g (3.13g), Mianmaguanzhong (*Dryopteris crassirhizoma* Nakai), 9g (1.88g), Tinglizi (*Descurainia sophia*(L.)Webb.ex Prantl.):15g (3.13g).

A previous retrospective cohort study showed that SHHS could considerably reduce the incidence of mild and moderate COVID-19 turning into severe disease (Tian et al., 2020). Although this study suggests that SHHS can prevent and treat COVID-19, there are no further randomized controlled clinical trials to confirm this. Therefore, we hypothesized that SHHS plays a therapeutic role no less than LHQW in patients with mild and moderate COVID-19. Consequently, we designed a randomized, parallel-controlled, open-label clinical trial to demonstrate the efficacy and safety of SHHS in the treatment of COVID-19. The primary objective of this study research is to describe a precise clinical study protocol and a predetermined statistical analysis plan.

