### Sample size

The study hypothesis is SHHS group will be non-inferior to LHQW group. Clinicians and statisticians set the non-inferiority threshold at 10% and predicted that the recovery rate of clinical symptoms after 7 days of LHQW is about 87% and that of SHHS is 90% according to the literature reports on similar drugs. It is estimated that 94 patients for each group, ie. a total of 188 patients are needed to achieve the power of 80% at a one-sided statistically significant level of 0.025. Considering the possible dropout rate of 20%, 240 patients will be enrolled, that is 120 patients for each group.

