## Statistical analysis plan

### Statistical methods

The statistical analysis plan will comply with the guidelines for the content of statistical analysis plans in clinical trials (Gamble et al., 2017). (**Additional File 3**). After finishing the trial, all statistical analysis tests will be conducted using SAS (version 9.4; SAS Inc., Cary, NC, USA) and one-sided tests with a nominal alpha level of 0.025. All confidence intervals (Cls) will be stated at the 95 confidence level. To assess non-inferiority, the CI lower limit of the difference between groups will be compared with a predefined non-inferiority limit. Non-inferiority could only be declared when the 95% CI lower limit of the difference between groups is not larger than the non-inferiority threshold of 10%.

Continuous outcomes will be described by calculating the mean, standard deviation, median, and minimum and maximum values. The means and standard deviations are reported for normal continuous data. For non-normally distributed continuous variables, the median and interquartile ranges are given. The frequency and proportion of each category are displayed as counting indications.

Between-group comparisons are performed using an independent two-sample t-test (normality, homogeneity of variance) or the Wilcoxon rank-sum test (non-normality, heterogeneity of variance). The paired t-test is used for comparisons within normally distributed groups, and the paired rank-sum test is used for comparisons within non-normally distributed groups. For count metrics, the χ^2^ test or Fisher's exact probability will be required, whereas, for categorical variables, the Wilcoxon rank-sum test will be utilized. Repeated measured outcomes are applied to a generalized linear mixed model analysis.

In patients where baseline indicators are unbalanced, an adjustment to the efficacy contrast of variables such as age, sex, and concurrent therapy is required. The covariance approach is employed for continuous variables, and for count or rank data, logistic regression analysis is performed.

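### The article says the trial will confirm the safety of SHHS, but Table 5 compares adverse events by P value alone, without the difference and 95% CI that Tables 3 and 4 carry.

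*Protocol article*

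**What the plan says.** Two statements set the safety aim. The Discussion part of the abstract says: "The results of this study will provide robust evidence to confirm the effectiveness and safety of SHHS in the treatment of COVID-19". The Introduction describes an "open-label clinical trial to demonstrate the efficacy and safety of SHHS in the treatment of COVID-19".

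The section Analysis of safety outcomes is mainly descriptive. It covers type, severity, frequency and relationship to the medicine, discontinuations, and a cross-tabulation. On comparison it says only this: "The quantity and frequency of adverse events are calculated for both groups". Table 5 then has three columns: SHHS n (%), LHQW n (%) and a P value. Its rows are total adverse events and five named terms. Tables 3 and 4, for the primary and secondary outcomes, place a difference with a 95% CI beside each P value. Table 5 does not.

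Statistical methods sets "one-sided tests with a nominal alpha level of 0.025" and adds "All confidence intervals (Cls) will be stated at the 95 confidence level". The second sentence fixes the level of any interval that is reported, but does not call for one on adverse events. The margin and the sample size concern symptom recovery only.

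**The concern.** *Confirm* and *demonstrate* are claims about what the data can rule out. For efficacy the plan respects this, since non-inferiority is judged by an interval set against a bound. For safety the same verbs are used, but the planned table gives no estimate of the difference and no measure of its uncertainty. The P value is its only comparative statistic.

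The number of patients was chosen for the recovery rate, so a non-significant adverse event comparison may carry little information. A report that follows Table 5 would let a reader see that no difference was significant, but not how large an excess on SHHS the data still allow.

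**Working it through.** **1. The plan's own figure.** The only sample size calculation is for efficacy. Its inputs, from Sample size, are a margin ("Clinicians and statisticians set the non-inferiority threshold at 10" per cent), recovery of 87% on LHQW and 90% on SHHS, one-sided 0.025 and 80% power.

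n per arm = (1.960 + 0.842)² × (0.87×0.13 + 0.90×0.10) / (0.10 + 0.03)² = 7.849 × 0.2031 / 0.0169 = 94.3

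The article gives 94. Allowing for 20% dropout, 94 / 0.80 = 117.5, and the article enrols 120 per arm. The figure reproduces, and nothing in it refers to adverse events.

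**2. What 120 per arm can show on adverse events.** The safety set needs one dose and one safety assessment, so 120 per arm is a fair upper figure. No test is named for safety. The article names chi-square or Fisher for count data elsewhere. In the direction of harm, one-sided 0.025 has the same cut-off as two-sided 0.05. No adverse event rate is stated, so the rates below are assumptions.

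Normal approximation, 5% v 10%:
- SE under no difference: √(2 × 0.075 × 0.925 / 120) = 0.0340
- SE under the alternative: √((0.05×0.95 + 0.10×0.90) / 120) = 0.0339
- Power = Φ((0.05 − 1.96×0.0340) / 0.0339) = Φ(−0.49) = 0.31, so the chance of missing the doubling is 69%.

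The exact figures sum the two binomial probabilities over all outcomes in which the test does not reject.

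Chance that a true doubling is non-significant, 120 per arm:

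| LHQW v SHHS (assumed) | Normal approx. | Chi-square, exact | Fisher |
|---|---|---|---|
| 1% v 2% | 91% | 93% | 99% |
| 2% v 4% | 85% | 87% | 94% |
| 3% v 6% | 80% | 81% | 89% |
| 5% v 10% | 69% | 68% | 78% |
| 8% v 16% | 52% | 52% | 60% |
| 10% v 20% | 42% | 41% | 48% |
| 15% v 30% | 20% | 20% | 24% |
| 20% v 40% | 7% | 7% | 9% |

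At 96 per arm (120 × 0.80), the chi-square and Fisher figures are 74% and 82% for 5% v 10%, and 50% and 58% for 10% v 20%.

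**3. What an interval would add.** With equal rates of 5%, the half-width of the 95% CI for the difference is 1.96 × √(2 × 0.05 × 0.95 / 120) = 5.5 points. At 10% it is 7.6 points. With no events in 120, the two-sided 95% upper limit for that arm is 1 − 0.025^(1/120) = 3.0%.

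As an illustration, suppose 6/120 on LHQW and 12/120 on SHHS. The test statistic is 0.05 / 0.0340 = 1.47, below 1.96 and so non-significant. The difference is +5.0 points with a Wald 95% CI of 5.0 ± 6.6, that is −1.6 to +11.6. Table 5 as laid out would show the counts and the P value but not that range.

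**The case against.** The strongest reply is that the plan sets no rule by which non-significance counts as safety. A reader might infer such a rule from the word *confirm* placed beside a P value, but the documents do not support that. The safety section is descriptive and relies on judgement, the only hypothesis is non-inferiority on recovery, and the strongest wording sits in the abstract's closing statement. This stands, and the point does not depend on such a rule.

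A reader might also infer that the trial should have had a safety margin or safety power. That does not follow. Neither is usual in a phase 2 trial sized for efficacy, and their absence is no error.

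A third tempting reading is that a relevant excess would usually be missed. That depends on the rate. At 10% v 20% the miss rate is 41% to 48%, so the excess is detected slightly more often than not. All the named terms in Table 5 except headache are also listed as symptoms in Tables 2 and 4, so their rates cannot be presumed to lie between 3% and 10%.

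Two further replies have some force. Anyone can compute the interval from the counts and percentages, so no information is lost. And a table shell in a condensed article may be fuller in the complete plan. Still, the article prints Table 5 as its chosen safety layout, gives the interval in the shells for the other outcomes, and makes the claim in its own text. If the full plan already has the interval, only the shell and the verbs need correcting.

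**Conclusion.** The point holds as a mismatch between claim and display. The article promises to confirm or demonstrate safety, and the planned comparison is a P value without an estimate or interval, which cannot support that promise.

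The size is conditional. For an assumed LHQW rate of about 3% to 10% and 120 dosed patients per arm, a doubling would be non-significant about 40% to 80% of the time by chi-square and about 48% to 89% by Fisher. Across both tests the figure is about 7% to 24% at 15% to 20%, and about 87% to 99% at 1% to 2%. The first band should not be quoted without its assumption.

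The efficacy analysis, its error rate and the sample size are unaffected. The change should be made because it bounds what the trial can say about safety at almost no cost.

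**What to change.** - In Table 5, replace or supplement the P value with the risk difference, SHHS minus LHQW, and its 95% CI (for example Miettinen-Nurminen). Do this for any adverse event, serious adverse events, adverse events leading to discontinuation, and each listed term.
- In the abstract and the Introduction, say that the trial will describe the safety of SHHS.
- Add one sentence to Analysis of safety outcomes: a non-significant difference in adverse events will not be taken as evidence of safety.
- In the same edit, reconcile the title of Table 5, which names the full analysis set, with the section text, which uses the safety set.

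The cost is one table column, a few added rows and a few sentences. Conduct and sample size do not change. The downside is a more modest safety claim.

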### Ethics and dissemination

The study protocol was approved by the Ethics Committee of the Affiliated Hospital of Changchun University of Traditional Chinese Medicine (no. CCZYFYLL2022). All participants will provide written informed consent. The results of this study will be published in peer-reviewed journals.

## Discussion

The ongoing COVID-19 pandemic, which has been spreading for more than two years, has led to various variants of SARS-CoV-2 (Tao et al., 2021; Khandia et al., 2022). The increased transmissibility or severity of SARS-CoV-2 continually poses serious challenges to vaccine development and targeted therapeutic strategies (Dong et al., 2021; Lino et al., 2022). Timely intervention with TCM in COVID-19 has been shown to significantly relieve symptoms, shorten the course, and improve the prognosis of the disease An et al., 2021. The trial is a randomized, active-drug parallel-controlled, open-label, non-inferiority clinical trial carried out in China to evaluate the effectiveness of SHHS compared to LHQW among patients with COVID-19. This phase 2 clinical trial will provide clinical evidence of TCM herbal preparations for preventing and treating COVID-19. The SAP was developed to prepare for statistical analysis of all data after the completion of this study and locking of the database. Although this is a single-center and open-label study, the quality of evidence will be improved by strict quality control and transparent reporting. The findings of this study will have important implications both for Chinese and western clinical practices. Furthermore, if the non-inferior conclusion could be declared in our study, SHHS granules will be confirmed its effects not only for symptoms management of COVID-19 and reducing the severe incidence, but also for extended indications of virus pneumonia or influenza. All of these depend on integrated multi-source high-quality data including randomized controlled trials and observational studies in the future.

## Data Availability

The original contributions presented in the study are included in the article/Supplementary Material further inquiries can be directed to the corresponding authors.
